## Abstract

**Background:**

Previous research suggests that both cognitive training and physical exercise help to maintain brain health and cognitive functions that decline with age. Some studies indicate that combined interventions may produce larger effects than each intervention alone. The aim of this study is to investigate the effects of combined cognitive and physical training compared to cognitive training and physical training alone on executive control and memory functions in healthy older adults.

**Objectives:**

The main objectives of this four-arm randomized controlled trial (RCT) are: to investigate the synergetic effects of a simultaneous, group-based multidomain training program that combines cognitive video-game training with physical exercise, in comparison to those produced by cognitive training combined with physical control activity, physical training combined with cognitive control activity, or a combination of both control activities; to investigate whether event-related potential latencies of the P2 component are shorter and N2 and P3b components assessed in a memory-based task switching task are enhanced after training; and to find out whether possible enhancements persist after a 3-month period without training.

**Methods:**

In this randomized, single-blind, controlled trial, 144 participants will be randomly assigned to one of the four combinations of cognitive training and physical exercise. The cognitive component will be either video-game training (cognitive intervention, CI) or video games not specifically designed to train cognition (cognitive control, CC). The physical exercise component will either emphasize endurance, strength, and music–movement coordination (exercise intervention, EI) or stretching, toning, and relaxation (exercise control, EC).

**Discussion:**

This RCT will investigate the short and long-term effects of multidomain training, compared to cognitive training and physical training alone, on executive control and memory functions in healthy older adults, in comparison with the performance of an active control group.

**Trial registration:**

ClinicalTrials.gov, NCT03823183. Registered on 21 January 2019.

## Background

Age-related cognitive decline affects negatively the performance of daily living activities and the quality of life of many older adults. Neurocognitive frailty is the principal threat to successful aging [1, 2] as cognitive performance is central for daily life [3]. Cross-sectional studies have reported declines in a series of cognitive abilities [4–7], although these declines are less pronounced in longitudinal studies [5]. Aging is associated with a progressive decline in a wide range of cognitive abilities, such as set shifting [6], working memory [4, 6], and episodic memory [5, 7, 8]. Yet other cognitive functions which rely on previous experience, such as vocabulary and general knowledge [4, 9, 10], procedural knowledge [11], and implicit memory [12–15], are mainly preserved, not only in healthy older adults but also in those with mild cognitive impairment [16], people with Alzheimer disease [14, 17], and older adults with type 2 diabetes mellitus [18].

Cerebral aging is associated with gray and white matter reduction in several areas of the brain, including the lateral prefrontal cortex, the cerebellum, and the medial temporal lobe system including the hippocampus. In contrast, minimal decreases occur in the entorhinal and occipital cortices [19]. The prefrontal cortex organizes the incoming information and interacts with the hippocampus while performing working-memory tasks [20, 21]. Cognitive-control functions refer to the ability to adapt behavior in order to process only relevant over competing irrelevant information to attain certain goals. Neuroanatomical changes occurring in the lateral prefrontal cortex and the medial temporal lobe–hippocampus complex are associated with declines in executive functions, working memory, and episodic memory. The failure of these basic cognitive functions predicts upcoming difficulties with the performance of daily-living activities and compromises independent living [22]. However, even in advanced age, the human brain preserves a certain degree of plasticity and functional reorganization, which allows people to adapt to age-related cerebral changes in order to maintain successful task performance [23–25]. Neuroplasticity in older adults is contingent on individual behavior [26–30] and is susceptible to be modified by interventions designed to delay or prevent age-related cognitive decline [31]. Brain plasticity and its role in neural adaptations to age-related cerebral changes are also influenced by comorbidities, environmental factors, personality traits (psychosocial variables), and genetic and epigenetic factors [32]. A recent *Frontiers Research Topic* monograph focused on research conducted in the field of cognitive and brain plasticity induced by physical activity, cognitive training (computerized interventions, learning therapy, video games), and combined-intervention approaches, as well as other forms of brain stimulation that target brain activity, such as electroencephalography and neurofeedback [33]. During the last two decades, researchers have conducted a variety of intervention studies directed to promote behavioral flexibility and to enhance several cognitive processes that decline with age. Indeed, evidence for the benefits of cognitive training, video games, and physical exercise is growing rapidly, as well as research directed at gaining a better understanding of the underlying mechanisms and their translation to clinical practice [34–36].

Cognitive training is an intervention that allows structured training in a series of tasks relevant to different cognitive functions, such as executive functions, speed of processing, episodic memory, cognitive control, or attention. Among cognitive psychologists and neuroscientists there is increasing interest in exploring whether cognitive training with specially designed computerized training programs and video games of different kinds enhances cognition. Video games are electronic games that require interaction with a computer or other electronic devices with a user interface that provides visual and auditory feedback. Computerized cognitive programs and video games are currently receiving great attention in exploring the possibility of transfer to untrained tasks [37–42]. Many intervention studies based on cognitive training support the idea that training in older adults improves some aspects of cognition but not others. In recent years, several meta-analyses [43–47] have examined the effectiveness of computer-based interventions in healthy older adults. These meta-analytic studies have shown low to moderate training effects in older adults in several cognitive processes that decline with age, such as processing speed, attention, and memory. However, others [48] have reported that playing video games had little consequences on cognition. Due to different study designs (e.g., the inclusion of active or passive control groups [49, 50]) and types of training (e.g., video games of different kinds, computerized cognitive programs [51–54]), results have been heterogeneous, making it difficult to reach solid conclusions [55].

In addition, other types of training such as physical activity of different kinds are also explored as a way to improve the physical and cognitive status. The term “physical activity” includes a large number of activities related to voluntary body movements [32]. A large body of evidence supports the beneficial effects of physical activity on executive functions and memory [56–61]. Although early physical activity intervention studies, which mainly centered on cardiovascular training, showed that cardiovascular activity produced increases in hippocampal volume in older adults while improving spatial memory performance [62, 63], other types of physical exercise, such as motor fitness and coordination training, also resulted in increased hippocampal volume in healthy older adults [60]. Complex physical activities such as dancing [64–66] or the practice of martial arts [67–71] have also shown beneficial effects on cognition in older adults.

Several studies suggest that social engagement plays a key role in the maintenance of cognitive functioning and psychological well-being in older adults [32, 72, 73] (for a recent review, see [74]). In the present multidomain intervention, social engagement is not considered a source of variance, as it is not a factor manipulated in the intervention, but, rather, a design feature included to enhance cognitive and physical functioning. So, cognitive and physical training, as well as their control activities, will be performed in a social environment. In this way, the four groups will be trained in the same social conditions; that is, in small groups and in the presence of a trainer.

### Objectives and hypotheses

The main objective of this randomized controlled trial (RCT) is to investigate the synergetic effects of a group-based multidomain training program that combines cognitive video-game training with physical exercise, in comparison to those produced by cognitive training combined with physical control activity, physical training combined with cognitive control activity, or a combination of both control activities, on behavioral and electrophysiological measures of executive control (set-shifting, response inhibition, and information updating and monitoring) and memory functions (immediate and delayed visual and verbal memory). These cognitive functions, which are often compromised in later years, are essential for everyday activities. The second objective is to investigate whether event-related potential (ERP) latencies of the P2 component are shorter and N2 and P3b components assessed in a memory-based task-switching task are enhanced after training. Electrophysiology provides a very useful online measure to identify the contribution of different processing stages of executive functioning. ERPs can help us to understand the specific executive control impairments occurring with age, as well as the possible effects of the different types of intervention investigated in this RCT. To this end, the task-switching paradigm is a valid task that helps to identify the cognitive processes that most decline with ageing [75]. However, electrophysiological studies conducted to evaluate training-related effects in older adults using this task are scarce [76]. Finally, we are interested in finding out whether possible enhancements persist after a 3-month period without training.

We expect to find greater behavioral improvements in executive control and memory functions after training, larger maintenance effects, and shorter ERP latencies of the P2 component and enhanced N2 and P3b components in the multidomain training condition in comparison to both single-domain conditions. We also expect the multidomain group and both single-domain groups to outperform the active control group at the 3-month follow-up period.

In this RCT, we will use questionnaire data to verify that the groups do not differ in their levels of intrinsic motivation and engagement. At the end of the assessment session, participants will report their expectations regarding their performance in the assessment tasks using a 5-point Likert scale. Moreover, at the 1st, 8th, and 16th training session, the participants will respond to questions about motivation and engagement for each of the training video games. These factors will be examined by comparing the intervention arms to the active control condition. The engagement and motivation data will be used in secondary analyses as covariates in order to rule out these factors as sources of variation in the primary outcome variables.

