### Sample size

We conducted an a priori power analysis using G*Power 3.1 [80] to calculate the appropriate sample size. Using an α value of 0.05, power of 0.80, and a medium effect size (*f* = 0.38) for video-game training [45] and physical training [81], and four groups within the *F*-test family, a total sample size of 124 is required. Considering a dropout rate of 12%, a total of 144 participants would be sufficient to detect significant main effects. According to this calculation, the adequate number of participants in each group (multidomain training, video-game training, physical activity training, and active control) is 36. According to this, we will set a sample size of 36 participants per arm, which is adequate for the experimental design. According to Montgomery et al. [82], with this number of participants the design would be underpowered to detect an interaction effect, as it would need a fourfold increase in sample size. However, given that lower interaction effects would not be clinically relevant, we decided to maintain our initial sample size estimation.

In the elaboration of this protocol, we have followed the SPIRIT 2013 explanation and elaboration guidance for reporting protocols of clinical trials [83].

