### Statistical analysis

All data from participants with complete baseline assessment and who attended at least one training session will enter into a primary intention-to-treat analysis. For the secondary per-protocol analysis, only the data of participants with a complete cognitive assessment and an attendance rate ≥ 70% will be considered.

Executive functions (set shifting, maintenance, inhibitory control) and memory functions (short-term, visual, and verbal immediate and delayed memory) will be assessed at pretest, posttest, and follow-up. The statistical analysis corresponding to the behavioral results will be carried out with the SPSS statistical package for Windows (SPSS 25.0; IBM Corporation). Results will be considered significant at *p* < 0.05, with Bonferroni-corrected post hoc tests performed as appropriate. We will explore the missing data to ascertain their pattern and will apply an adequate technique of multiple imputation. Repeated ANOVA measures will be conducted with four groups (multidomain training, cognitive training, exercise training, active control) at three time points (pretest, posttest, follow-up) to test the primary hypothesis (i.e., differences in efficacy between interventions compared to the active control condition). Repeated ANOVA measures will also be performed to determine the effect of the interventions on secondary outcomes. To evaluate the effect size of the combined multimodal group versus each individual intervention group and the control arm, we will use multimodal regression with an interaction term. Electrophysiological data will be analyzed with CURRY 8.0.2, the EEGLAB toolbox [92], and the ERPLAB plugin for EEGLAB [98].

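### The plan would verify that arms do not differ in motivation and engagement, but its only stated criterion is a difference test, and a non-significant result cannot show that

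*Protocol article*

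**What the plan says.** The Objectives and hypotheses section states the aim as a conclusion of no difference: "we will use questionnaire data to verify that the groups do not differ in their levels of intrinsic motivation and engagement". The method follows shortly after: "These factors will be examined by comparing the intervention arms to the active control condition". The data come from repeated ratings: "at the 1st, 8th, and 16th training session, the participants will respond to questions about motivation and engagement for each of the training video games". The same section gives the data a second use: "The engagement and motivation data will be used in secondary analyses as covariates in order to rule out these factors as sources of variation".

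Neither a margin nor a difference of interest is attached to the check. The one decision criterion in the article is in the Statistical analysis section: "Results will be considered significant at *p* < 0.05", "with Bonferroni-corrected post hoc tests performed as appropriate". The Sample size section sets 36 participants per arm, to detect main effects on the outcomes. It does not address this check.

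**The concern.** To verify that groups do not differ is an equivalence claim. A difference test starts from equality and asks whether the data contradict it. Failing to reject may mean that the arms are alike, or only that the arms are small. Bonferroni protects against false claims of a difference, so if it were applied here it would make a false claim of no difference more likely.

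The matter is not idle. The General procedure section says that the active control is there to control for placebo effects. The two kinds of game also differ in character: the intervention games are adaptive and commercially designed for brain training, while the control games are word and trivia games. Unequal engagement is plausible, and it is a rival explanation that a reader of the results will raise. If the report answers that the groups were verified not to differ, the answer should carry weight.

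**Working it through.** **Inputs from the article.** 36 per arm; 124 participants required before the dropout allowance, which is 124/4 = 31 per arm; significance at 0.05 (taken as two-sided, since sidedness is not stated); Bonferroni for post hoc tests; three comparisons, each intervention arm against active control.

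**Assumed, not in the article.** A benchmark difference of 0.5 SD; one rating per person; independent participants.

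**The plan's own figure.** A one-way ANOVA with f = 0.38, four groups, α = 0.05 and power 0.80 needs N = 80, not 124. N = 124 gives about 95% power. The dropout step is consistent: 124/0.88 = 140.9, so 141, rounded up to 4 × 36 = 144. The mismatch over 124 is a separate matter. Only the arm sizes are used below.

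**Chance of missing a 0.5-SD difference.** With n per arm, the standard error of a difference in SD units is √(2/n), and the noncentrality is 0.5/√(2/n).
- n = 36: SE = 0.236, noncentrality 2.12.
- n = 31: SE = 0.254, noncentrality 1.97.

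The miss rate is one minus the power of the two-sided noncentral t test on 2n − 2 degrees of freedom.

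| | 36 per arm | 31 per arm |
|---|---|---|
| α = 0.05 | 45% | 51% |
| α = 0.05/3 = 0.0167 | 62% | 68% |
| Four-group F test, one arm shifted 0.5 SD | 44% | 51% |

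**What a non-significant result leaves open.** The half-width of the 95% interval is t × SE: 1.994 × 0.236 = 0.47 SD at 36 per arm and 2.000 × 0.254 = 0.51 SD at 31. Even an observed difference of zero is compatible with a true difference of roughly half an SD in either direction.

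**Other readings of the plan (α = 0.05).**
- Three intervention arms pooled against control: SE = √(1/n + 1/(3n)), which is 0.192 or 0.207. The miss rate is 27% at 36 per arm and 33% at 31.
- Three sessions averaged, with 0.5 SD referring to a single session and correlation ρ between sessions: the standardised difference becomes 0.5/√((1 + 2ρ)/3). The miss rate is 27–34% at ρ = 0.5 and 42–48% at ρ = 0.9.

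The article specifies neither.

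**Chance of demonstrating comparability when the true difference is zero.** With an illustrative margin of ±0.5 SD, the normal approximation is 2Φ(0.5/SE − z) − 1.
- 90% interval (z = 1.645): 2Φ(2.12 − 1.645) − 1 = 37% at 36 per arm; 2Φ(1.97 − 1.645) − 1 = 25% at 31.
- 95% interval (z = 1.96): 2Φ(2.12 − 1.96) − 1 = 13% at 36 per arm; close to zero at 31, where the expected half-width of 0.51 already exceeds the margin.
- Pooled by game type, 90% interval: about 82% with 72 against 72 and about 74% with 62 against 62.

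**The case against.** The strongest reply is that the rule under criticism is inferred. The Objectives section names no test and no alpha for this check; it speaks only of examining and comparing. The p < 0.05 and Bonferroni sentence sits among the behavioural outcomes and does not mention motivation or engagement. A margin could be in an analysis plan that is not shown. All of this stands, so the point must be conditional: if the only stated criterion is applied, the conclusion does not follow. It does not dispose of the point, because the aim as worded already commits to a conclusion of no difference, and nothing in the article supplies a criterion that could support it.

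Second, the covariate analyses are the stated means of ruling out these factors, and they do not depend on the outcome of the check. So a reader who infers that the trial's case against a motivational explanation rests on this check alone goes further than the article does. Still, adjusting for ratings does not show that the arms are equal, and the ratings are taken during training, after randomisation.

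Third, the numbers depend on choices. A reader might infer that the check would usually report no difference when the arms differ by 0.5 SD. At the planned 36 per arm without correction, it would detect that difference slightly more often than not. The stronger reading needs Bonferroni, whose use here is not stated, or about 31 per arm, where it holds only barely. A correction for all six pairwise comparisons would not match the planned arm-versus-control comparisons. Nor does the article show that a half-SD gap in motivation would be enough to produce a cognitive training effect.

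**Conclusion.** The point holds in a limited form. The stated aim and the only stated criterion do not fit together: a non-significant difference cannot verify that the groups do not differ. Under a pairwise test of one rating per person, a 0.5-SD difference goes undetected 45–51% of the time without correction and 62–68% with Bonferroni for three comparisons. These rates rest on the assumed benchmark, a two-sided test and 31–36 participants per arm, and they fall under pooling or averaging. The logical gap is there at any of these rates.

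The consequence is confined to what the report may say about comparability of motivation and engagement. No primary estimate, test or sample size changes. The wording should be corrected, but the trial's main conclusions do not hang on it.

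**What to change.** Replace the aim of verifying that the groups do not differ with wording such as: *Differences between each intervention arm and active control in motivation and engagement will be estimated and reported with 95% confidence intervals, without multiplicity correction. A non-significant difference will not be taken as evidence of comparability. Comparability will be claimed only if the interval lies within a margin set by the investigators in advance.*

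The margin is for the investigators to choose and justify; the ±0.5 SD used above is only an illustration. Because the ratings concern the video games, a comparison pooled by game type (the two cognitive-intervention arms against the two cognitive-control arms) may be added. It should supplement the arm-level comparison with active control, not replace it, since pooling says nothing about, for example, multidomain against cognitive training alone.

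The cost is wording, plus agreement on a margin; no new data are needed. The drawback is that arm-level comparability will often not be demonstrable even if the arms are truly alike: about a 25–37% chance at ±0.5 SD with a 90% interval, and lower with the 95% interval proposed here. In that case the report gives the estimates and their intervals and makes no claim of comparability.

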### Study design

Participants will complete one of the four combinations of cognitive training with video games and physical exercise. The cognitive component will be either a brain-training video-game program selected from Lumosity (cognitive intervention, CI) or video games not specifically designed to train particular cognitive functions such as attention, memory, or executive control (cognitive control, CC). The physical exercise component will be either a senior-friendly adaption of BODYATTACK™ (https://www.lesmills.com/), a combination of dance, aerobic, strength, and muscular resistance (exercise intervention, EI), or its control condition comprising stretching, toning, and relaxation (exercise control, EC). The duration of sessions for all groups will be the same, and all participants will perform physical exercise and video-gaming activities in a social environment (in small groups formed by 10–12 participants) and in the presence of the trainer.

To summarize, the study will have a 4 × 3 mixed factorial design with four intervention conditions—multidomain (CI + EI), uni-domain cognitive intervention (CI + EC), uni-domain physical intervention (EI + CC), and active control (CC + EC)—assessed at three different time points (pretest, posttest, 3-month follow-up), with “Type of training” as between-subject factors and “Time” as the within-subject factor. The dependent variables will be behavioral and/or electrophysiological measures of executive functions (inhibition, shifting, working memory), memory functions (short term and long-term visual and word memory), and emotional well-being, quality of life, and motivation.

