### Randomization and blinding

After the baseline assessments, participants will be randomly allocated to one of the four training protocols in a stratified process using the online tool Random Lists (move this to the other linehttps://www.randomlists.com/). [name] will generate the random sequence and will assign participants to interventions. At first, participants who came in couples will be randomly allocated as a unit to one of the four groups, and afterward the same procedure will be performed with the individual participants. This procedure aims to minimize dropouts due to separating couples in different groups. Participants and exercise instructors will be blinded to treatment allocation (single-blind). Data analysis will not be blinded, as it will be performed by the investigators who actively collaborate in the study. We do not envision any reason why participants should be unblinded, either during the trial or at the end of the study.

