#### Cognitive intervention

In each session, participants in the CI group will play 10 video games selected from the commercial Lumosity computerized training program (http://lumosity.com/). Lumosity provides a series of games targeting the improvement of several cognitive functions. Table 1 presents a short description of the games and their trained domains. These functions are sensitive to age-related cognitive decline and closely related to the ability to perform activities of daily living, such as driving. The participant will play the games in a predetermined sequence, for approximately 5–10 min for each game. Each participant in the CI group will have a Lumosity user account assigned. These games are adaptive—meaning that as performance improves, the difficulty increases, progressively adjusting to the participant’s performance level.

**Table 1 Tab1:** Short description of the video games for the cognitive intervention

Game name	Trained function	Description
Train of Thought	Divided attention	The player directs trains to their matching station
Assist Ants	Divided attention	The player prevents collisions by placing obstacles in their paths
Trouble Brewing	Divided attention	The player simultaneously serves orders to different customers
Playing Koi	Divided attention	The player keeps track of which fish has already been fed, in a square of randomly appearing fishes
Memory Serves	Working memory and divided attention	The player matches different pieces of luggage to their corresponding owners
Disillusion	Flexibility	The game consists of matching tiles with different shapes, colors, or symbols
Ebb and Flow	Flexibility	The player swipes in the direction to which the leaves are moving or pointing
Master Piece	Spatial reasoning	The player reorientates a shape so that it fills a hollow section
Speed Pack	Visualization	The player has to fit the last item into an already filled suitcase
Highway Hazards	Information processing	The player dodges obstacles in a race through a virtual desert

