#### Cognitive control activity

The cognitive control component will exclusively involve language-specific processes and crystalized knowledge (see Table 3). These domains are preserved with age, and even though an implication of executive functioning cannot be ruled out, this is clearly not the main active component. The cognitive control games are available within the gaming service Google Play Games, which mimics cognitive training platforms. This will create the impression of receiving an intervention, thereby reducing expectation biases. Participants will play 10–15 min each game in a predetermined sequence.

**Table 3 Tab3:** Short description of the video games for the cognitive control condition

Game name	Trained function	Description
Hangman	Lexical access	The player guesses a word by suggesting letters within a certain number of guesses
Grammar	Lexical access	The player chooses the correct spelling of a word within three possibilities
Definitions	Semantics and lexical access	The player chooses the correct word according to a given definition
Word search	Lexical access	The player identifies words hidden in a grid filled with letters
Crossword	Semantics and lexical access	The player constructs words by solving clues
Synonyms and antonyms	Semantics and lexical access	The player produces a word with a similar or opposite meaning of a given word
Trivia quiz	Crystalized knowledge	The player answers to questions of general knowledge

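### Motivation and engagement ratings taken during training cannot, as covariates in the secondary analyses, rule these factors out as an explanation for arm differences

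*Protocol article*

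**What the plan says.** Four places in the protocol article bear on this point.

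- **Timing of allocation** (Randomization and blinding): "After the baseline assessments, participants will be randomly allocated to one of the four training protocols".
- **Timing of the ratings** (Objectives and hypotheses): "at the 1st, 8th, and 16th training session, the participants will respond to questions about motivation and engagement", asked separately for each video game. The Interventions section gives 16 sessions in all, so these are the first, the middle and the last.
- **Purpose** (Objectives and hypotheses): the questionnaires are meant to "verify that the groups do not differ in their levels of intrinsic motivation and engagement". Then: "The engagement and motivation data will be used in secondary analyses as covariates in order to rule out these factors as sources of variation", with the primary outcomes named as the variables concerned.
- **Status of motivation** (Study design): the list of dependent variables ends "and emotional well-being, quality of life, and motivation".

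The rated games depend on allocation. Under Cognitive intervention, "participants in the CI group will play 10 video games selected from the commercial Lumosity computerized training program", and these are adaptive: "as performance improves, the difficulty increases". Under Cognitive control activity, "The cognitive control component will exclusively involve language-specific processes and crystalized knowledge". The Statistical analysis section tests the primary hypothesis by a repeated-measures ANOVA of four groups at three time points and names no covariate.

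**The concern.** A covariate measured before randomisation can be adjusted for without changing what the arm contrast estimates. A covariate measured afterwards can itself be changed by the arm. Here it is a rating of the allocated activity, and the protocol also lists motivation among its outcomes.

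Whether gains come from training or from motivation is a central question for a trial with an active control group. The stated analysis would answer it with a model that supports the answer only under an assumption the article does not mention. An effect that shrinks after adjustment could be put down to motivation when it is not, and an effect that survives or appears after adjustment could be credited to training without warrant.

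**Working it through.** **Order of events.** Baseline assessment comes first, then allocation, then session 1, session 8 and session 16. All three ratings are post-randomisation. No rating of motivation or engagement with the games before allocation is described.

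**What the adjustment does.** For two arms and a linear model, let *a* be the arm difference in mean engagement and *s* the pooled within-arm slope of outcome on engagement. Then

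adjusted contrast = unadjusted contrast - *a* x *s*.

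The slope *s* has two possible sources: a causal effect of engagement on the outcome (*b*), and unmeasured causes common to both. With unit-variance engagement and a shared cause loading *g* on engagement and *h* on the outcome, *s* = *b* + *g* x *h*. Arm, engagement and outcome data alone do not separate the two.

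**Inputs.** From the documents: 36 per arm (Sample size). The documents give no value for *a*, *b*, *g* or *h*, so all of these are assumed: *a* = 0 to 0.8 SD, *b* = 0 or 0.3, *g* = *h* = 0 or 0.5. The check was a simulation of two arms of 36 with 4,000 replicates, least squares with and without the engagement covariate, and a two-sided 5% level. Effects are roughly in SD units.

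1. *Arm does not affect engagement* (*a* = 0, *b* = 0.3, *g* = *h* = 0.5, true effect 0.5). Unadjusted 0.499, adjusted 0.496. No bias.

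2. *Engagement mediates and there is no shared cause* (direct effect 0.4, *b* = 0.3, *g* = *h* = 0):

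| *a* | total = 0.4 + 0.3*a* | simulated unadjusted | simulated adjusted | power unadjusted | power adjusted |
|---|---|---|---|---|---|
| 0.2 | 0.46 | 0.456 | 0.399 | 0.45 | 0.38 |
| 0.5 | 0.55 | 0.555 | 0.403 | 0.61 | 0.36 |
| 0.8 | 0.64 | 0.637 | 0.397 | 0.73 | 0.32 |

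The adjusted model recovers the direct effect. That is a different quantity from the randomised total effect, so the two power columns do not refer to the same target.

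3. *True arm effect zero, engagement has no effect on the outcome, shared unmeasured cause* (*b* = 0, *g* = *h* = 0.5, so *s* = 0.25):

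| *a* | -*a* x 0.25 | simulated adjusted | type I error, adjusted |
|---|---|---|---|
| 0.2 | -0.050 | -0.047 | 5.1% |
| 0.5 | -0.125 | -0.123 | 8.5% |
| 0.8 | -0.200 | -0.204 | 13.0% |

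The unadjusted estimate stays within 0.003 of zero, and its type I error lies between 4.8% and 5.2%.

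In cases 2 and 3 the same operation, subtracting *a* x *s*, is right for the direct effect in one and wrong in the other. Which case applies depends on the unmeasured causes.

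**Does the planned check for equal groups settle it?** With 36 per arm, the 95% half-width for a pairwise difference is about 1.96 x sqrt(2/36) = 0.46 SD before dropout. A non-significant difference would leave moderate differences in engagement open.

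**The case against.** The strongest reply has four parts.

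- **The adjustment is secondary.** This stands. The primary ANOVA names no covariate, so the randomised comparison is intact. A reader might infer that the trial's main arm comparison is biased; the documents do not support that.
- **An arm effect on engagement is not shown.** This also stands. The control games were chosen to resemble a training platform, all groups train under the same social conditions, and the article expects no group difference. A reader might infer that the ratings are certainly mediators, or attach a percentage of the effect lost. The documents give no values from which to derive either, and any honest range starts at zero.
- **The difference in games does not apply to every contrast.** This is correct. The multidomain and cognitive-only arms rate the same Lumosity games, and the physical-only and active control arms rate the same control games. The argument from different rated content applies to comparisons across the two cognitive components.
- **Removing the part that runs through motivation is the purpose, not an error.** This is fair as far as it goes: case 2 shows the direct effect recovered. It holds only without shared causes of engagement and outcome. Prior ability or general drive could be such causes, and randomisation of arms does not balance them across levels of engagement.

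What remains is the stated inference. If arms do not differ in engagement, there is no imbalance to remove. If they do, the adjusted contrast needs an unstated and untested assumption before it says anything about motivation.

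**Conclusion.** The point holds as a fault in a stated secondary analysis and the conclusion to be drawn from it. Post-randomisation ratings of the allocated games are to be used as covariates to exclude motivation as an explanation, and that analysis cannot by itself exclude or establish it. The same construct also appears as a dependent variable, a role the article does not reconcile with its use as an adjustment covariate.

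The conclusion rests on the order of events and on the linear identity above. Size and direction cannot be fixed from the documents. Distortion is nil if arm does not affect engagement; the simulated figures illustrate the mechanism under assumed values and do not estimate it for this trial. The matter is worth correcting because the claim concerns the primary outcomes and the repair is cheap, but it does not threaten the primary analysis.

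**What to change.** - Keep the contrast without these covariates as the effect estimate for the primary outcomes.
- Report motivation and engagement by arm with confidence intervals for the arm differences. The comparison with the active control is already planned; the intervals would replace reliance on a non-significant difference.
- Replace the covariate analysis and its claim of exclusion with one labelled exploratory mediation. State the assumption of no unmeasured common causes of engagement and outcome, and add a sensitivity analysis for its violation. The adjusted model need not be dropped.
- Limit covariate adjustment of the effect estimate to variables measured before allocation, such as the baseline outcome. The expectation rating qualifies only if it is obtained before allocation; the article does not say which assessment session collects it.

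No new data are needed, and the article describes the trial as ongoing, so the wording could be settled before results are known. The cost is some extra analysis and a weaker claim about mechanism.
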